### Assessment – Secondary endpoints

#### Postural control

A force plate (Leonardo Mechanograph®, Novotec medical, Pforzheim, Germany) is used to assess changes in the center of pressure during upright static and dynamic stance. The assessment follows a standardized protocol (see Table 1). Primarily, the supporting foot is determined with a short test [36]. Patients are asked to maintain an upright position with their knees slightly flexed (~30°), hands at their side and their gaze straight ahead for 30 s. The cumulative change in sway paths during this period is registered and serves as a measure of postural control. To minimize bias through potential learning effects, each position is repeated three times. Additionally, failed attempts are recorded should a patient seek hold. The tasks become progressively more difficult as previous studies (see reference [37] for review) have shown that postural tasks with different complexity serve best to test for changes in stance stability after balance training. To assess the dynamic stance, a balance pad is additionally placed on top of the force plate.

#### Questionnaires

##### FACT/GOG-Ntx - questionnaire

The particular sector of the FACT/GOG-Ntx [Functional Assessment of Cancer Therapy/Gynaecology Oncology Group – Neurotoxity] is used to document and assess the severity of the subjective PNP symptoms [38]. This questionnaire has been validated and contains eleven items which allow an assessment of the extent of PNP symptoms – from “not at all” to “very much” [25].

##### EORTC-QLQ-CIPN20

The EORTC-QLQ-CIPN20 is a phase IV questionnaire that we are evaluating for [name] in the course of this study. It is a 20-item questionnaire that was developed to elicit patients’ experience of symptoms and functional limitations related to CIPN.The CIPN20 has 3 subscales: a sensory, a motor, and an autonomic subscale.

##### EORCT-QLQ-C30

The EORTC-QLQ-C30-questionnaire is used to assess health-related quality of life. In addition to a scale for “global quality of life”, the questionnaire contains five functional scales (physical, emotional, social and cognitive functions, and role functions), three symptoms scales (fatigue, pain, nausea/vomiting), and single item scales of respiratory distress, insomnia, loss of appetite, constipation, diarrhoea, and financial problems. The questionnaire has been validated and translated into 81 languages and has been used in more than 3000 studies worldwide. It is internationally regarded as reliable [39, 40].

##### PainDETECT

This questionnaire focuses on pain specifically related to PNP. It helps assess patients’ subjective experience of neuropathy-related pain. The questionnaire includes 12 items that take the intensity, progression, and distribution of pain into account. The questions are answered on a Likert scale ranging from “not at all” to “very much”, which are summed up to yield a total score that reflects neuropathic pain status. Pain DETECT is a validated and reliable screening tool with high sensitivity, specificity and positive predictive accuracy [41, 42].

##### FFKA

Physical activity levels are evaluated using the Freiburger Physical Activity Questionnaire (FFKA), a standardized and validated questionnaire that assesses the physical activities performed by a patient during the past 4 weeks. Based on the patients’ answers, MET-scores are calculated [43, 44].

See Table 1 for Flow-chart of all assessments.

### Training program

The interventions start immediately after randomization and are continued throughout the entire medical therapy (~3 to 6 months). Training sessions are supervised and take place twice a week in specific training rooms designed to meet the needs of oncological patients in an outpatient setting or during the hospital stay, in one of the centers. Each session lasts for about 15 to 30 min. Depending on the type of intervention, the training will involve:**Sensorimotor training** consists of progressively more difficult balance exercises on progressively instable surfaces. Each patient performs 4 exercises per session following a standardized protocol (see Table 1). Each exercise is performed three times for 20 s, allowing a 40 s rest between each set and a 3-min rest between each exercise, to avoid neuronal fatigue. Patients are asked to stand barefoot or in socks, their foot in a previously acquired “short-foot-position”, knees slightly flexed (30°), and to maintain balance.**Vibration training** takes place on a vibration platform (Galileo™, Pforzheim, Germany)®. Each training session consists of four sets of 30 s to 1 min vibration. The frequency of the vibrating platform ranges between 18 and 35 Hz with a 2 mm amplitude. Between sets, the patients rest for at least 1 min to avoid fatigue. Patients are asked to stand on the platform barefoot and on their forefeet or if they are too instable, an 80/20% distribution of weight on the forefeet rather than the heels.

Each training session allows for individual progression within a standardised selection of exercises (see Table 1) and is documented by the sports therapist.

### Statistical procedures and sample size estimation

Central computerized randomisation (RITA) using a modified minimization procedure with stochastic component according to Pocock and Simon is performed [45]: intervention 1: intervention 2:control = 1:1:1, stratified by study center and type of therapy (Oxaliplatin, Vinca-alkaloids). In trials under similar conditions, a balanced randomization has been achieved using this algorithm [14].

Sample size calculation is based on the primary endpoint incident CIPN. Power calculation is based on the following scenario: The assumed incidence rate with TAU is 90%, which was informed by a review of the literature. In both intervention groups, we assumed an incidence rate of 75%. The effect size corresponds to a relative risk of about 0.60, which is a clinically meaningful effect size. Using the log-rank test (1-β = 0.8, two-sided α = 0.05), we need a total of 196 evaluable patients, 65 per group [46, 47]. We anticipate a drop-out rate of 10%, yielding a total of 236 patients to be recruited for this study, 79 per group. This calculation is conservative as we may achieve additional power performing the final analysis using a multivariable Cox proportional hazards regression model adjusting for study center, type of chemotherapy, type of cancer, gender, and age.

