**Methods:**

We are therefore conducting a prospective, multicentre, controlled clinical trial involving 236 oncological patients receiving either oxaliplatin (*N* = 118) or vinca-alkaloid (N = 118) who are randomized to one of two interventions (SMT or WBV) or a treatment as usual (TAU) group. Primary endpoint is the time to incidence of neurologically confirmed CIPN. Secondary endpoints are pain, maintenance of the functionality of sensory as well as motor nerve fibres as well as the level of physical activity. The baseline assessment is performed prior to the first cycle of chemotherapy. Subsequent follow-up assessments are conducted at 12 weeks, after completion of chemotherapy, and at a 3-month follow-up. Patients who develop CIPN receive an additional assessment at this time point, as it represents the primary endpoint.

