## Methods/design

### Study participants and recruitment

We plan to enrol 236 newly diagnosed haematological/oncological patients who are scheduled to receive chemotherapy containing either oxaliplatin or a vinca-alkaloid, aged ≥18 years, with the mental and physical ability to provide signed informed consent and participate in the study. Patients are recruited at three participating centres: The University Hospital of Cologne, the St. Antonius Hospital in Eschweiler and the joint practice for oncology and hematology at the Sachsenring in Cologne. Exclusion criteria is a pre-existing neuropathy of other cause. Therefore, patients will be assessed clinically for signs of neuropathy and will undergo nerve conduction studies prior to randomization. Neuropathy will be defined electrophysiologically as CMAP amplitude below 5 mV, SNAP amplitude below 5 μV, and nerve conduction velocity below 40 m/s of tibial or sural nerve). Further exclusion criteria are previous therapies containing neurotoxic agents, any contraindication for whole body vibration (instable bone metastases, acute leg thrombosis, a fracture in the lower extremities in the past 2 years, foot ulcers, artificial hips or other osteosynthesis), and myocardial infarction, angina pectoris or heart disease (NYHA III-IV) within the past six months.

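### 196 evaluable patients and 10% drop-out give 218 patients to recruit, not 236, so either the drop-out rate or the recruitment total is misstated

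*Protocol article*

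**What the plan says.** The calculation is in the protocol article, section Statistical procedures and sample size estimation. Allocation is equal across three arms ("intervention 1: intervention 2:control = 1:1:1"). The design values are introduced with "Using the log-rank test (1-β = 0.8, two-sided α = 0.05", and the result is "we need a total of 196 evaluable patients, 65 per group". The next sentence moves from evaluable to recruited patients: "We anticipate a drop-out rate of 10%, yielding a total of 236 patients to be recruited for this study, 79 per group".

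The total is used elsewhere as the size of the trial. The section Study participants and recruitment says "We plan to enrol 236 newly diagnosed haematological/oncological patients". The abstract describes a "controlled clinical trial involving 236 oncological patients receiving either oxaliplatin" or a vinca-alkaloid, with 118 in each chemotherapy group (118 + 118 = 236).

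**The concern.** The sentence presents 236 as the result of applying a 10% drop-out rate to 196. A reader who repeats that step gets a number about 18 lower. The enrolment target in the abstract and in the participants section rests on this step.

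Two things are at stake. The first is how much attrition the plan was meant to absorb. With 236 enrolled, the trial can lose 236 - 196 = 40 patients and still have 196 evaluable; 10% of 236 is only about 24. Anyone later judging whether losses exceeded the plan needs to know which allowance applies. The second is the justification of the total. If 10% is correct, the stated inputs support 218, and the remaining 18 patients are recruited without a stated reason.

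**Working it through.** **Inputs**, all from the section Statistical procedures and sample size estimation: evaluable patients 196 (65 per group), drop-out rate d = 0.10, recruitment total 236 (79 per group).

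**1. Attempt to reproduce 236 from the stated inputs.**
- Standard inflation, N/(1 - d): 196/0.90 = 217.8, so 218.
- Shortcut, N x (1 + d): 196 x 1.10 = 215.6, so 216.
- By group, standard: 65/0.90 = 72.2, so 73 per group and 219 in total.
- By group, shortcut: 65 x 1.10 = 71.5, so 72 per group and 216 in total.

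None gives 236. The shortfall is 17 to 20 patients, which is more than rounding can produce.

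**2. Drop-out rate implied by 236.**
- From the totals: 1 - 196/236 = 16.9%.
- From the group sizes: 1 - 65/79 = 17.7%.
- As an uplift: 236/196 - 1 = 20.4%. A 20% uplift gives 196 x 1.20 = 235.2, which rounds up to 236.

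**3. Evaluable patients if 236 are recruited and 10% are lost.**
- 236 x 0.90 = 212.4, so about 212, or about 71 per group. That is 16 more than the 196 required.

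**4. A possible second allowance.**
- Applying 10% twice gives 196 x 1.21 = 237.2 or 196/0.81 = 242.0. Neither is 236, and the sample size section states no second loss.
- The section Recruitment of patients mentions refusals and drop-out only in explaining the patient numbers expected at the centres. It does not inflate the 196.

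**5. Size of the discrepancy.**
- 236 - 218 = 18 patients; 18/218 = 8.3% (18/236 = 7.6%).

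**The case against.** The strongest reply is that the discrepancy is harmless. It errs on the safe side: at the stated 10% loss the trial would have about 212 evaluable patients against a requirement of 196. No power is lost, and neither the type I error nor the estimates are affected. This stands, and it limits the weight of the point. What remains is a derivation that is wrong as printed and a total that exceeds what its stated inputs support.

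It could also be said that an article condenses a fuller protocol. That does not help here, because nothing is left out: all three numbers are printed and they disagree. Nor does a slip in a single figure look likely for the total, since 236 is repeated in two other places and agrees with 79 per group.

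Three stronger readings are tempting, and the document does not support them.

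- *The evaluable number behind the power claim is unknown.* It is not: the text ties 80% power directly to 196 evaluable patients. Only the step from 196 to 236 is unclear.
- *The per-group figures are a further error, because 3 x 65 = 195 and 3 x 79 = 237.* These are ordinary rounding: 196/3 = 65.3 and 236/3 = 78.7.
- *The total must not be reduced to 218 because 65 per group already falls short of 80% power.* That depends on the comparison, which the sample size section does not name. The stated incidences of 90% and 75% give a hazard ratio of ln(0.25)/ln(0.10) = 0.602 under proportional hazards. By Schoenfeld's formula, one intervention against control with 65 per arm (130 x 0.825 = 107 events) has about 75% power. Both interventions pooled against control (196 x 0.80 = 157 events, split 2:1) has about 85%. The drop-out arithmetic cannot settle that question.

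**Conclusion.** The point holds as an arithmetic inconsistency. The stated inputs give 218 patients to recruit (216 by the shortcut), and the article prints 236. The printed total matches about 17% loss or a 20% uplift, not 10%. The exact match at 20% suggests one possible origin, but the article does not say so.

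The conclusion takes 196 as given and reads the sentence as it is written, with 236 following from 196 and the drop-out rate. It needs no assumption about the test, the contrast or the hazard ratio. The excess is 18 patients, about 8%, in the direction of over-recruitment. This is a definite error in the sample size justification and should be corrected, but it is not a threat to the validity of the trial.

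**What to change.** The sponsor should state which figure was intended and correct the one sentence.

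- **If 236 is kept**, write either that the total allows for about 17% loss, leaving 196 evaluable, or that 10% loss leaves about 212 evaluable (about 71 per group). This costs one sentence and does not change recruitment.
- **If 10% is kept as the basis for the target**, the stated inputs give 218. The total would then also have to change in the abstract, including its split of 118 and 118, and in the section Study participants and recruitment.

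The arithmetic does not favour one option over the other. Before choosing, the sponsor would do well to name the comparison to which the 196 refers, since the adequacy of 196 is a separate matter that bears on whether any reduction is sensible.

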#### Nerve conduction studies

For nerve conduction studies, motor and sensory nerves are assessed. Compound muscle action potentials (CMAP), distal motor latency, conduction velocity, and F-waves are obtained from the tibial nerve. The tibial nerve is stimulated at the ankle and popliteal fosse. Antidromic sensory nerve conduction studies are performed in the sural nerve. Sensory nerve action potentials (SNAPs) are recorded from the lateral malleolus with surface electrodes. Skin temperature is monitored and maintained above 32 °C using a heater if necessary.

We furthermore conduct a standardized neurological clinical test battery that is a feasible assessment method for oncological patients in order to check for first neuropathic symptoms. It is used as a pretest to screen for CIPN related symptoms. Should one of the components show irregularities, a neuroelectrography is required in order to detect and document a possible CIPN.

The test battery contains the following assessments:**Peripheral deep sensitivity** is evaluated by the use of a Rydel-Seiffer tuning fork (128 Hz) with a scale from 0 to 8. Due to age related neural deconditioning, values ≤4 are pathological for patients ≥60 years old, while for patients under 60 years old, ≤5 is regarded as pathological [34].**The Reflex action** of the Achilles- as well as the patellar tendon is assessed with a reflex hammer and graded on a 3-point scale (1 = agile, 2 = weak, 3 = missing).**Sense of position** is assessed by asking patients if they can recognize a change of position in their first toe, with their eyes closed.**Perception of touch** is evaluated by symmetrically stroking the outsides of the patients’ legs and feet in order to detect reduced or altered sensation due to demyelination or axonal degeneration [30, 35].**The strength of the lower leg muscles** is assessed by requesting the patient to actively move their legs against the resistance of the examiner’s arm. The examiner then grades the strength on a six-point scale (0 = no activity, 1 = visual contraction without motor effect, 2 = movement under elimination of gravity, 3 = movement under gravity, 4 = movement against slight resistance 5 = normal force).

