#### Data management and analyses

Data entry is continuously monitored by a data manager (TN) and will be analyzed by a statistician (ML). For the primary endpoint incident CIPN, censoring will be taken into account by using log-rank tests, and multivariable Cox proportional hazard regression models will be used to test for differences between groups and to estimate treatment effects. For categorical secondary endpoints, Fisher’s exact test and Wilcoxon signed-rank tests and multivariable logistic regression models will be performed. For continuous outcomes (including scores derived from self-report questionnaires), t-tests and multivariable linear or median regression models will be used. Multivariable models will adjust for study center, type of chemotherapy, type of cancer, gender, and age. Intention-to-treat analyses will be conducted based on complete cases and on multiply imputed data using a conditional imputation [48].

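### The covariates fixed for the primary Cox model leave out any baseline nerve conduction value, so the additional power the plan hopes for may be partly forgone

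*Protocol article*

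**What the plan says.** The abstract of the protocol article states: "Primary endpoint is the time to incidence of neurologically confirmed CIPN".

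Under Statistical procedures and sample size estimation, the sample size is set with the log-rank test: "Using the log-rank test (1-β = 0.8, two-sided α = 0.05". The same paragraph calls the calculation conservative because further power may come from the final analysis, a "multivariable Cox proportional hazards regression model adjusting for study center, type of chemotherapy, type of cancer, gender, and age".

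Data management and analyses repeats the list for every regression, primary and secondary: "Multivariable models will adjust for study center, type of chemotherapy, type of cancer, gender, and age". It also says that Cox models will be used both to test for group differences and to estimate treatment effects.

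On the measurement itself, Study participants and recruitment says that "patients will be assessed clinically for signs of neuropathy and will undergo nerve conduction studies prior to randomization", and Table 1 marks neuroelectrography at T0. Under Nerve conduction studies, when a component of the clinical test battery is irregular, "a neuroelectrography is required in order to detect and document a possible CIPN".

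**The concern.** The article does not leave the covariate list to a later document. It states the list twice, in the same terms. The list holds both minimisation factors plus cancer type, gender and age, but no baseline reading from the examination that helps to document the event. Every patient is due to have that reading before allocation.

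In a Cox model, leaving out a prognostic covariate pulls the treatment hazard ratio towards 1 and costs power. Minimisation covers only centre and type of therapy. A chance imbalance in baseline nerve status across three arms of about 65 evaluable patients would therefore be neither balanced by design nor adjusted for.

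At stake is efficiency on the primary comparison, in the model that the article presents as its reserve of power.

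**Working it through.** **Inputs from the article.** Cumulative incidence: "The assumed incidence rate with TAU is 90" per cent, and "In both intervention groups, we assumed an incidence rate of 75" per cent. Two-sided 5% level, 80% power, log-rank test, 65 evaluable patients per group, 1:1:1 allocation.

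**Inputs not in the article, so assumed.** The hazard ratio for CIPN per SD of the baseline nerve conduction value (1.0 to 2.0), and the correlation of that value with age (0.5 in absolute value).

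**Step 1: the plan's own figures.**
- Hazard ratio: ln(1 − 0.75) / ln(1 − 0.90) = (−1.386) / (−2.303) = 0.602. This agrees with the stated effect of about 0.60.
- Schoenfeld events, one intervention against TAU: 4 × (1.960 + 0.842)² / (ln 0.602)² = 122. Per group: 122 / (0.90 + 0.75) = 74, or 222 in three arms.
- Freedman events: (1.960 + 0.842)² × (1.602 / 0.398)² = 128. Per group: 128 / 1.65 = 78, or 233 in three arms.
- Neither pairwise formula reproduces the stated 65 per group and 196 in total. A three-arm log-rank test with 2 degrees of freedom comes closest: it needs 168 events and about 210 patients, and has simulated power of 0.787 at 195 patients. That mismatch is a separate matter and does not depend on the covariate list.
- Pairwise power at 65 per group: expected events 65 × (0.90 + 0.75) = 107.25. Power = Φ(√(107.25 / 4) × 0.5074 − 1.960) = Φ(0.667) = 0.748.

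One intervention against TAU therefore starts from about 75%, so extra power from adjustment is not a luxury.

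**Step 2: simulated effect of adding the baseline value.** Exponential event times, 65 versus 65, follow-up ending at a fixed time. The intercepts were solved so that marginal incidence stays at 90% and 75%. Wald test at 1.96, 3,000 runs per setting, giving a Monte Carlo standard error of about √(0.8 × 0.2 / 3000) = 0.007 per entry. In the first two result columns age is in both models, which is closer to the planned analysis.

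| Assumed HR per SD | Age only | Age + baseline value | Gain (points) | No age: without → with baseline value |
|---|---|---|---|---|
| 1.0 | 0.745 | 0.745 | 0.0 | 0.740 → 0.736 |
| 1.25 | 0.756 | 0.773 | 1.7 | 0.766 → 0.790 |
| 1.5 | 0.793 | 0.849 | 5.6 | 0.758 → 0.837 |
| 2.0 | 0.837 | 0.939 | 10.2 | 0.800 → 0.928 |

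The conditional treatment hazard ratio is re-solved in each row (0.602, 0.589, 0.561, 0.502) to hold the marginal incidences. Rows should therefore be read across, not down.

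A second simulation assumed a correlation of 0.4 with age and ran 1,000 to 1,500 replicates. It gave 0.774 → 0.796, 0.776 → 0.814 and 0.820 → 0.958 at hazard ratios per SD of about 1.31, 1.49 and 2.10. These are gains of about 2, 4 and 14 points.

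**Step 3: cost when the covariate is useless.** In the first row, power is unchanged to within Monte Carlo error. Expected events in three arms of 65 are 65 × 0.90 + 2 × 65 × 0.75 = 58.5 + 97.5 = 156, so one more parameter is affordable.

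**Limits.** Neither simulation includes centre, chemotherapy type, cancer type or gender. Both use exact event times, whereas the scheduled test battery is run every 6 weeks.

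**The case against.** The strongest reply is that a reader might infer too much. It is tempting to say that confirmation of CIPN rests on the sural SNAP, that patients entering just above 5 µV are bound to cross into the event sooner, and that power is therefore certainly lost. The article does not support this, for three reasons.
- Confirmation follows an abnormal clinical battery (tuning fork, reflexes, position sense, touch, strength). Patients' symptom reports and physicians' questions also bring cases forward. The neuroelectrography covers tibial motor measures as well as the sural nerve.
- The 5 µV limit is one of several values defining pre-existing neuropathy for exclusion. It is not given as the rule for incident CIPN. The article does not say whether that rule is an absolute cut-off or a change from baseline. The near-the-limit argument needs an absolute cut-off, and under a change rule the baseline value may predict less.
- No prognostic strength is given. Age, which is already in the model, may carry part of the same information.

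All of this stands, and it makes the size of the gain conditional. It also stands that the existing list is a coherent pre-specified set, that the plan says only that it may gain power, and that chance imbalance in an unlisted covariate does not invalidate a randomised comparison.

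The reply does not remove the case for the change. The value is already to be collected, and the simulations show no loss when it turns out not to be prognostic.

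**Conclusion.** The point holds as a conditional, low-cost improvement. The pre-specified covariates for the primary Cox model omit any baseline nerve conduction value, and power may be forgone as a result. Nothing stated in the plan becomes wrong because of the omission, since the 80% refers to the unadjusted log-rank test.

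With age in the model and a correlation of 0.5 assumed, the gain is about 0 to 10 points over a hazard ratio of 1.0 to 2.0 per SD. It is under 2 points at 1.25 and between 5 and 6 points at 1.5. These figures rest on proportional hazards, the plan's 90% and 75%, 65 per arm, one intervention against TAU, and a prognostic strength that the article does not supply. A flat claim that power is lost would go beyond the documents.

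**What to change.** Before unblinding, make two edits.
- In Statistical procedures and sample size estimation, add a baseline nerve conduction value to the covariates of the Cox model for time to CIPN. One candidate is the pre-randomisation (T0) sural SNAP amplitude, log-transformed and continuous. It is an example: the Background describes sensory nerves as especially sensitive, but the measure chosen should suit whatever electrophysiological rule confirms incident CIPN.
- In Data management and analyses, leave the general covariate sentence as it is, because it also governs the secondary-endpoint models. Add a sentence limited to the primary model, for instance: the Cox model for time to CIPN will additionally adjust for log baseline sural SNAP amplitude.

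The log-rank test and the secondary models stay unchanged. No new data, visits or patients are needed. The cost is one extra parameter, and a treatment hazard ratio that is also conditional on baseline nerve status.
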